At the start of session 2, participants will be familiarized with the rVMA protocol (familiarization set) by performing 20 trials of non-rotated ( $0^\circ$ ) practice trials. Afterwards, a non-rotated baseline condition set (104 trials) will be performed. After the baseline set, the EX groups (i.e., EX-DCD and EX-TD) will perform a 13-min iE session while the CON groups (i.e., CON-DCD and CON-TD) will rest the same period of time reading or holding a conversation, no additional exercise or musical activity will be permitted. Next, all participants will do an adaptation set (312 trials) in the rVMA task, with a clockwise rotation of  $60^\circ$  applied to the cardinal coordinates of the cursor movement. At one hour after the end of the adaptation set, all participants will perform a  $60^\circ$  clockwise retention set (short-term retention, RT1h, 104 trials). At the end of session 2, all participants will perform a memory game with the cards they collected during the 20mSRT and potentially the iE.

Sessions 3 and 4 will occur 24 h and 7 days from the end of the adaptation set. In each session, participants will perform a  $60^\circ$  clockwise rotated retention set (mid and long term retentions, RT24h, and RT7d respectively, 104 trials each).

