### **The rotational visuomotor adaptation task (rVMA)**

During the rVMA participants will be seated in a quiet room, in front of a 19-inch computer screen located at 1m and at eye level. With their dominant hand, participants will be asked to grasp a joystick, maintaining a claw-type grip, an elbow flexion of  $90^\circ$  and a comfortable shoulder position while the forearm rests on a flat surface (Figure 2a). The height and position of the joystick will be adjusted to meet the position criteria. The joystick movement controls a green dot on the screen (1x1cm). Individual targets will randomly appear on screen as red dots (1x1cm) in eight possible locations (45, 90, 135, 180, 225, 270, 315 and  $360^\circ$ ) and at a radius distance of 13 cm from the center. A new target will appear every 2 s and will remain visible for 750 ms. Participants will be instructed to move the green dot, starting from the center of the screen, over the target (red dot) and back to the center as fast and as straight as possible in a single move. During the task a visual-motor mismatch between joystick movement and screen cursor movement is applied by rotating the movement of the cursor, so the greater the rotation the greater the deviation of the cursor according to the movement of the joystick (for example see Ferrer-[name] et al., 2018). Cartesian x-y coordinates of the joystick movement and time will be registered at 120Hz through a NI-6008 card (National Instruments Corporation).

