### **Data reduction**

Data of the 20mSRT will be used to characterize participants' fitness level and to define the intensity of the exercise during iE performance in the second session. Individual maximum velocity ( $V_{max}$ , km/h) will be calculated using the last completed stage ( $E_{max}$ ) (Léger et al., 1988).

$$V_{max} = 0.5 \cdot E_{max} + 8$$

$VO_2max$  will be estimated based on the participant  $V_{max}$  and age ( $y$ , years) (Léger et al., 1988):

$$VO_{2max} = 31.025 + (3.238 \cdot V_{max}) - (3.248 \cdot y) + (0.1536 \cdot y \cdot V_{max})$$

Individual heart rate (HR) will be monitored by a Polar RS800CX (Polar Electro) and it will be synchronized with the time of the 20mSRT test (session 1) and with the iE intervals (session 3). Maximal HR (HRmax) during the childhood and adolescence periods is typically above 200 b/min. Therefore, we will use this value as a reference to assess maximal effort level in the last part of the 20mSRT (Armstrong & Fawcner, 2007). In addition, the mean HR during the iE intervals (85% and 60% of the estimated VO2max) will be calculated (HR-85%VO2max and HR-65%VO2max). These values will be used to further characterize the exercise's intensity during the iE.

The rVMA data fitting and reduction will be done using custom-made MATLAB R2014b programs (The MathWorks, Inc.). Cartesian x-y positions will be low-pass filtered using an eight-order dual-pass Butterworth filter with a cut-off frequency of 12Hz. Accepted trials will have to fulfill the following conditions: startup position found within 20% of the center-to-target distance, and travelled distance equal or higher to 90% of the center-to-target distance. Movement onset of the accepted trials will be defined as the nearest point in an outward movement equal to a 10% of the center-to-target distance. Movement offset will be defined as the first point where speed decreased to a 10% of the max speed value. The adaptation set will be divided in epochs of 8 trials for analysis purposes.

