## Variables

The movement during the rVMA task will be described by the calculated movement time (MT, ms), travel distance (TD, cm) and reaction time (RT, ms) variables. RT will be defined as the time between target appearance and movement onset. Movement output error will be measured through the initial directional error (IDE, deg) and root mean square error (RMSE, cm) variables (Figure 5). IDE will be calculated as the absolute angular difference between the ideal trajectory, a linear vector from the center to the target, and the early real trajectory, defined by the linear vector from the center to the green dot position at the time of 80 ms after movement onset. IDE will be used as a measure of the rotation adaptation or motor consolidation avoiding the possible trajectory correction through perceptual feedback (Contreras-Vidal et al., 2005; Ferrer-[name] et al., 2018, 2017). RMSE will be calculated to represent the straightness of the movement between the ideal trajectory and the real joystick trajectory following the procedure described in Contreras-Vidal et al. (2005):

$$RMSE = \sqrt{\sum_{i=1}^N [(x_1 - x_2)^2 + (y_1 - y_2)^2] \frac{1}{N}}$$

where  $(x_1, y_1)$  and  $(x_2, y_2)$  are the coordinates of the real and ideal trajectory, respectively, and  $N$  is the number of points in the path. Movement straightness (i.e., RMSE) includes the initial deviation from the ideal trajectory (IDE) and the remaining movement trajectory, which could be corrected using perceptual feedback. All these variables will be calculated for each set (baseline, adaptation, RT1h, RT24h, and RT7d). Considering the large inter-subject variability usually presented by children, computed mean adaptation and retention variables will be normalized by subtracting the participant's mean baseline values.

It is proposed that DCD groups will show more variability than their TD peers (King, Haring, Oliveira, & Clark, 2011; Roche et al., 2016; Smits-Engelsman & Wilson, 2013). Inter-trial variability will be calculated via SD for all performance variables in the rVMA (MT, MT-SD, TD, TD-SDRT, RT-SD, IDE, IDE-SD, RMSE, and RMSE-SD) to characterize the groups.

During the adaptation set, data typically present an initial rapid-error decay followed by a slower decline. As it has been seen in other studies (Ferrer-[name] et al., 2018, 2017; Krakauer, Ghez, & Ghilardi, 2005), these data from adaptations seem to be best fitted by a double exponential function:

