We will compare the mean baseline value for each rVMA and brain hemodynamics variables with ANOVAs to evaluate baseline performance across the four groups. Differences between the CON-DCD and CON-TD children groups (O1.2 and O2.1) on the motor learning (adaptation and retention phases) will be explored using independent t-tests in the adaptation set, while 2 (Group) x 3 (Time) ANOVAs with repeated measures will be used to analyze differences in the retention phases. Focusing on the effects of exercise (O1.3 and O2.2), possible differences in the adaptation set will be contrasted by 2 (Group) x 2 (Exercise) ANOVAs and retention tests will be analyzed by 2 (Group) x 2 (Exercise) x 3 (Time) ANOVAs with repeated measures. Association of the changes in brain activation variables with changes occurred in the rVMA variables will be explored using bivariate correlations and multivariate correlations (O2.3). Usability and additional information provided by fNIRS and fDCS will be evaluated qualitatively and contrasted brain activity levels obtained from both technologies using t-test and ANOVAs (adaptation: t-test (Technology); retention tests: 2 (Technology) x 3 (Time) ANOVAs) (O3).

Before any statistical test normality distribution will be tested for all variables via exploration of histograms, Q-Q plots and with the Shapiro-Wilk's normality test. When the normality assumption failed, variable transformation or non-parametric alternative tests will be adequately conducted. In all ANOVAs Greenhouse-Geisser sphericity-corrected values will be used when appropriate. Variables with initial group differences and significantly correlated with the dependent variable will be considered as potential covariates in the ANOVA analyses. Bonferroni *post hoc* analyses will be performed if significant differences are found. In addition, the effect size will be calculated using  $\eta^2p$  (0.01 small, 0.06 medium, 0.14 large effect). Statistical significance was set at  $p < 0.05$  for all analyses.

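### Each retention test is scored as one mean over 104 rotated feedback trials, so it mixes retention with relearning within the set and, at 24 h and 7 days, with practice from earlier tests

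*Protocol*

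**What the plan says.** Under Experimental protocol, children first complete the rotated learning phase: "Next, all participants will do an adaptation set (312 trials) in the rVMA task". One hour later comes a 60° "clockwise retention set (short-term retention, RT1h, 104 trials"), followed in later sessions by the "mid and long term retentions, RT24h, and RT7d respectively, 104 trials each".

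The task section says that "The joystick movement controls a green dot on the screen (1x1cm") and that "During the task a visual-motor mismatch between joystick movement and screen cursor movement is applied by rotating the movement of the cursor". It describes no trials without feedback, and no catch trials, for any set.

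Under Data reduction, "The adaptation set will be divided in epochs of 8 trials for analysis purposes". Nothing equivalent is stated for the retention sets. Under Variables, "All these variables will be calculated for each set (baseline, adaptation, RT1h, RT24h, and RT7d"), and the retention means are then normalised by subtracting the child's baseline mean. Rate of learning and rate of variability are defined for adaptation only. Under Statistical analysis, "retention tests will be analyzed by 2 (Group) x 2 (Exercise) x 3 (Time) ANOVAs with repeated measures". The DCD-TD comparison in the control groups uses a 2 x 3 version of the same model.

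**The concern.** What a child has retained shows in the first trials of a retention test. After that the child again sees errors under the rotation and can learn from them. A mean over the whole set combines starting level and speed of relearning, and no other retention measure in the protocol separates the two.

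H1 names both quantities. It predicts a slower rate of learning and worse consolidation in children with DCD, and an exercise benefit on consolidation. For adaptation, it cites a null exercise effect in TD children and makes no prediction for DCD. The retention score therefore carries the behavioural exercise hypothesis and half of the DCD-TD contrast. If it also reflects relearning speed, a DCD deficit on it cannot be attributed to consolidation.

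The three tests are also taken in sequence by the same children, so RT24h and RT7d come after extra practice and the Time factor is not a pure retention interval.

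**Working it through.** The protocol gives no figure to reproduce here. The trial counts are its own; every time constant, error level and SD below is an assumption.

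**1. Trial counts** (Experimental protocol, Data reduction)
- Epochs per retention set: 104/8 = 13. First epoch as a share of the score: 8/104 = 7.7%.
- Retention set relative to adaptation: 104/312 = one third.
- Rotated trials done beforehand: RT1h 312; RT24h 312 + 104 = 416 (+33%); RT7d 312 + 208 = 520 (+67%).

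**2. How much of a first-trial difference survives in the mean**

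Assume the difference decays fully and exponentially with time constant τ trials. The share kept in a mean over n trials is (1/n) Σ exp(−t/τ), t = 0 to n−1.

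| τ (trials) | whole set, n = 104 | first epoch, n = 8 |
|---|---|---|
| 8 | 0.08 | 0.67 |
| 16 | 0.16 | 0.81 |
| 24 | 0.23 | 0.87 |
| 40 | 0.36 | 0.92 |
| 65 | 0.50 | 0.95 |
| 104 | 0.64 | 0.97 |
| 312 | 0.85 | 0.99 |

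The whole-set share falls below one half only when τ is under about 64 trials (8 epochs).

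**3. Equal recall, different relearning speed**

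Suppose two groups both start a retention set at 30° error and approach 10°, one with τ = 24 trials and the other with τ = 40.
- Whole-set means: 10 + 20 × 0.233 = 14.7° and 10 + 20 × 0.361 = 17.2°. Difference 20 × (0.361 − 0.233) = 2.6°, although recall is identical.
- First-epoch means: 10 + 20 × 0.868 = 27.4° and 10 + 20 × 0.918 = 28.4°. Difference 1.0°.

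The early measure reduces the artefact but does not remove it.

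**4. Is the first epoch a more sensitive outcome?**

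Take a 5° exercise difference in the first epoch, a between-child SD of 10° in the decaying component and 5° in the asymptote, and a trial SD of 20°. Let w be the whole-set share divided by the first-epoch share: 0.195, 0.268 and 0.393 at τ = 16, 24 and 40.
- First epoch: 5/√(10² + 5² + 20²/8) = 0.38.
- Set mean, difference decays fully: 5w/√((10w)² + 5² + 20²/104) = 0.17, 0.22 and 0.30.
- Same formula at τ = 104 (w = 0.657): 0.39.
- Set mean, half of the difference persists: (2.5 + 2.5w)/√((10w)² + 5² + 20²/104) = about 0.52 at all three of the shorter time constants.

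The ranking of the two measures therefore depends on the assumptions.

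**The case against.** The strongest reply is that the protocol supplies no relearning rate. The rapid initial fall in error that it describes belongs to first exposure in the adaptation set. A child returning after 312 rotated trials may start near plateau and have little to relearn. The protocol also models adaptation with two exponentials, and a difference in the slow component may outlast 104 trials. This stands. A reader might infer that the retention scores mostly measure relearning, or that the first epoch is clearly the more powerful outcome; the documents support neither, as steps 2 and 4 show.

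Two further limits stand. Carry-over from earlier tests cannot affect RT1h, which has none before it. And EX and CON complete identical sets within each cohort, so the randomised comparison is not biased. A reader who infers a biased exercise effect goes too far.

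The first epoch has weaknesses of its own. Eight trials give a noisier mean. Targets appear at random in eight locations, so an epoch may miss some directions. Trials can be rejected on start position or distance travelled, and the first trials after a break include warm-up.

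One defence does not succeed. Reading IDE 80 ms after movement onset limits correction within a movement, not learning from one trial to the next; RMSE, by the protocol's own account, includes movement that feedback may have corrected. Nor is this merely a detail left to an analysis plan: the protocol itself sets the epochs, the per-set mean and the model.

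**Conclusion.** The point holds in limited form. As defined, the retention score cannot separate retention from relearning within the set, and at RT24h and RT7d it also reflects 104 and 208 additional rotated trials. These facts need no assumption about learning speed.

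The main consequence is for DCD versus TD, where H1 itself predicts a difference in learning rate: equal recall could be read as poorer consolidation, by about 2.6° under the illustrative values in step 3. For exercise versus rest the comparison remains valid; the effect may be diluted and its reading as consolidation is less secure. More than half of an initial difference is lost only if it decays fully and the time constant is below about 64 trials, and the protocol does not show whether either condition is met. That supports adding an early-trial measure, not discarding the set mean.

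**What to change.** - In Data reduction and Variables, divide RT1h, RT24h and RT7d into 8-trial epochs, as is already done for adaptation.
- Pre-specify the first epoch of each set as a retention measure, with the first two epochs as a sensitivity analysis. Analyse it in the same Group x Exercise x Time ANOVA, alongside the whole-set mean.
- Report the change over the later epochs separately, as relearning.
- Base statements about consolidation, above all for DCD versus TD, on the early-epoch measure and not on the set mean alone.
- State that Time reflects retention interval plus accumulated practice (312, 416 and 520 prior rotated trials).

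The cost is analysis wording only, since the planned sets already yield these trials. The price is the noise, incomplete target coverage, rejected trials and warm-up in an 8-trial mean, which is why the whole-set mean is kept.

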### **The rotational visuomotor adaptation task (rVMA)**

During the rVMA participants will be seated in a quiet room, in front of a 19-inch computer screen located at 1m and at eye level. With their dominant hand, participants will be asked to grasp a joystick, maintaining a claw-type grip, an elbow flexion of  $90^\circ$  and a comfortable shoulder position while the forearm rests on a flat surface (Figure 2a). The height and position of the joystick will be adjusted to meet the position criteria. The joystick movement controls a green dot on the screen (1x1cm). Individual targets will randomly appear on screen as red dots (1x1cm) in eight possible locations (45, 90, 135, 180, 225, 270, 315 and  $360^\circ$ ) and at a radius distance of 13 cm from the center. A new target will appear every 2 s and will remain visible for 750 ms. Participants will be instructed to move the green dot, starting from the center of the screen, over the target (red dot) and back to the center as fast and as straight as possible in a single move. During the task a visual-motor mismatch between joystick movement and screen cursor movement is applied by rotating the movement of the cursor, so the greater the rotation the greater the deviation of the cursor according to the movement of the joystick (for example see Ferrer-[name] et al., 2018). Cartesian x-y coordinates of the joystick movement and time will be registered at 120Hz through a NI-6008 card (National Instruments Corporation).

### **The intense exercise bout (iE)**

The intense exercise (iE) bout will consist of a 13-minute 20-meter shuttle run. During this exercise bout two speeds, based on a percentage of the estimated  $VO_{2max}$ , will be combined: a fast-paced speed (fast, 85% of  $VO_{2max}$ ) and a slow-paced speed (slow, 60%  $VO_{2max}$ ). A total of 3 series of 3 min of the fast-paced speed will be carried interspersed with 2 series of 2 min of the slow-paced speed. Prior to the iE start, a warm-up protocol consisting of 2 min slow and 1 min fast will be done with the objective to familiarize participants with the iE speeds. A 5-minute rest period will be guaranteed before starting the iE. Transition time between iE and rVMA will be 4 min. Participants' heart rate will be captured following the same procedure described for the 20mSRT.

## **Optical neuroimaging: The functional Near-Infrared Spectroscopy (fNIRS) and the functional Diffuse Correlation Spectroscopy (fDCS) protocol**

During sessions 2, 3, and 4, 27-channel NIRS instrument (Brite MKII, Artinis Medical Systems, Netherlands) will be placed in the head of the participants to perform recordings of the hemodynamic changes of their right and left dorsolateral pre-frontal cortex (DLPFC), ventrolateral pre-frontal cortex (VLPFC), and oculo pre-frontal cortex (OPFC) to cover motor, perceptual and attentional areas. Placement of the optodes and cap will be anchored to various landmarks in the 10-20 EEG electrode placement system (Cao et al., 2015). Participants will be asked to rest seated during 30 seconds before the familiarization, baseline, and adaptation sets (session 2), the RT24h (session 3) and the RT7d (session 4) to record a reference resting state in the fNIRS signals before to start the rVMA task. In the pilot study to explore the usability of a fNIRS and fDCS hybrid device, DCS sensors will be placed closer to fNIRS sensors to perform simultaneous recordings of the areas defined previously. Both devices will be placed at the same time and their recording will be synchronized.

The Brite MKII is a portable wave continuous system developed to measure concentration changes of oxyhemoglobin ( $[O_2Hb]$ ) and deoxyhemoglobin ( $[HHb]$ ), which indirectly reflect brain activity. The light sources (optodes) transmit two wavelengths,  $\pm 760$  nm and  $\pm 850$  nm, and the receiver is a high sensitive PIN diode with ambient light protection. The distance between the receiver and the optodes and the sensitive PIN diode and the intensity of the light can be modified to better adjust to participant characteristics. Spring-loaded grommets will be used to improve data quality in dark thick hair. Data acquisition sampling rate will be set to 10 Hz. Oxysoft software (v6.0, Artinis Medical Systems, Netherlands) will allow real time assessment of the quality of the fNIRS signals and zero baseline will be set when acceptable signal-to-noise ratio was obtained. In the pilot study, fDCS will measure cerebral metabolic rate of oxygen extraction ( $CMRO_2$ ), and microvascular cerebral blood flow (CBF) during all motor task phases to assess short and long-term changes in cortical processing. Data acquisition sampling rate of the hybrid device (fNIRS and fDCS) will be set at the same frequency when they collect data together. fNIRS and fDCS data will be analyzed using programs wrote by our team and our collaborators in ICFO.

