fNIRS and fDCS data, will be converted into changes in concentration levels of oxyhemoglobin ([O2Hb]), deoxyhemoglobin ([HHb]), cerebral metabolic rate of oxygen extraction (CMRO2), and microvascular cerebral blood flow (CBF). A subject-specific differential path-length factor (DPF) will be used for this conversion based on the age of the participant (Duncan et al., 1996; Scholkmann & Wolf, 2013). Data will be low-pass filtered to avoid excessive frequencies that will belong to normal physiology activity and noise from respiration and heart beats or movements (typically a cut-off frequency of 0.1 Hz). Filtered data will be normalized relative to the individual values found in the reference resting state measures. All these processes previous to calculate the variables will be computed using custom made programs.

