$$y = a * e^{b*x} - c * e^{d*x}$$

where  $y$  is the error (epoch's mean),  $x$  is the epoch number and  $a$ ,  $b$ ,  $c$  and  $d$  are parameters. The initial rate of learning (RL) will be computed, as described in Coats (2014), as the first derivative of the first half of the function and evaluated at epoch 1 for both error variables IDE (RL-IDE) and RMSE (RL-RMSE). All individual exponential functions will be visually inspected for a plateau to assess that learning is achieved.

Progress towards increasingly skilled performance consists of the acquisition and stabilization of more effective movement patterns (Vereijken, Van Emmerik, Bongardt, Beek, & Newell, 1997). Inter-trial variability could be used to assess the stabilization level of the task. High values of variability are related to an early learning stage that explores new solutions for the task while low values of variability are associated with more skilled performers showing stable executions. Changes in variability across epochs in the acquisition set (i.e., rate of variability, RV) for both error variables (RV-IDE-SD and RV-RMSE-SD) will be also computed.

Normalized changes in concentration levels of hemodynamic variables during the different sets will be analyzed. Neural activation of each cortical area will be expressed as an increase of  $[O_2Hb]$  (also of  $CMRO_2$  and CBF in the pilot study) and a decrease in  $[HHb]$  (Mandrick et al., 2013). Qualitative analysis of the changes in these variables across trials will be performed to establish differences in hemodynamic patterns. Average and SD of the hemodynamic variables for each set will be calculated.

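### The 1-hour retention set is the only task set without its own 30-second fNIRS reference rest, so its optical values rest on a reference at least 70 minutes old, while RT24h and RT7d each have a fresh one

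*Protocol*

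**What the plan says.** The Optical neuroimaging section names the sets preceded by a reference rest; children are to "rest seated during 30 seconds before the familiarization, baseline, and adaptation sets (session 2), the RT24h (session 3) and the RT7d (session 4". The purpose is "to record a reference resting state in the fNIRS signals before to start the rVMA task". The list goes set by set, not session by session: session 2 alone has three rests, one of them before the short familiarization set. RT1h is not listed.

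RT1h belongs to session 2. The Experimental protocol section places it there: "At one hour after the end of the adaptation set, all participants will perform a" rotated retention set. Optical recording covers that session ("During sessions 2, 3, and 4, 27-channel NIRS instrument"), and the Variables section summarises every set: "Average and SD of the hemodynamic variables for each set will be calculated".

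The Data reduction section gives the normalisation rule: "Filtered data will be normalized relative to the individual values found in the reference resting state measures". It makes no exception for RT1h and does not pair rests with sets. The Statistical analysis section then analyses retention with a three-level repeated Time factor: Group x Time in the CON children for O2.1, and Group x Exercise x Time in all children for O2.2.

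**The concern.** The device records changes in concentration, so a normalised value depends on the rest it is compared with. Two of the three retention levels have a rest taken just before the set. The third has none and must use one from before the adaptation set or earlier. A difference between RT1h and the later retention sets then mixes two things: a change in cortical activation, and a change in how old the reference is. Hypothesis H2 concerns how activation changes over adaptation and consolidation, so this comparison matters.

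A second problem may follow, depending on which earlier rest is used. The nearest is the one before adaptation. In EX it comes shortly after the 13-minute run, since "Transition time between iE and rVMA will be 4 min". In CON it comes after 13 minutes of sitting quietly. If that rest serves as the RT1h reference, the reference differs between randomised arms at one Time level and not at the other two.

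**Working it through.** **Inputs, all from the protocol.** Adaptation set 312 trials, baseline set 104 trials, RT1h 60 min after the end of adaptation (Experimental protocol). One target every 2 s (rVMA section). Exercise 13 min, pause of 5 min before it, warm-up 2 + 1 = 3 min, transition 4 min (intense exercise bout section). 30 children per cell, so 60 EX and 60 CON (Participants). The protocol states no figure for reference age, so there is none to reproduce.

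**Age of the reference at each retention set**
- RT24h and RT7d: the rest directly precedes the set, so about 0 min.
- RT1h with the pre-adaptation rest: 312 x 2 s = 624 s = 10.4 min; 10.4 + 60 = 70.4 min at least.
- RT1h with the pre-baseline rest, EX: the baseline set lasts 104 x 2 s = 208 s = 3.5 min; 3.5 + 5 + 13 + 4 + 10.4 + 60 = 95.9 min, or 98.9 min if the 3-min warm-up is also counted.
- RT1h with the pre-baseline rest, CON: 3.5 + 13 + 10.4 + 60 = 86.9 min at least. The protocol does not say whether the pause and transition minutes also apply to CON.
- The pre-familiarization rest is older again.

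**What each choice does.** Assume normalisation by subtraction; the protocol does not say whether it subtracts or divides.
- Signal drift of d between an old reference and RT1h, equal in all groups: RT1h moves by d and the other levels by 0. This appears as a Time effect of d, with no Exercise x Time effect.
- Pre-adaptation rest used, and still shifted by x after exercise in EX only: the EX-CON difference moves by -x at RT1h and by 0 at RT24h and RT7d. The contrast of RT1h with the mean of the other two moves by -x, and the Exercise main effect moves by (-x + 0 + 0)/3 = -x/3.
- A pre-exercise rest used: x does not enter. Only the drift term remains.

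**Illustration of the second case only.** Compare EX with CON, 60 each, on the contrast RT1h minus the mean of RT24h and RT7d, two-sided 5%, true effect zero. With unit SD at each set and a common correlation rho between sets, the contrast SD is sqrt(1 + (1 + rho)/2 - 2 rho), which is 1.02, 0.87 and 0.67 for rho = 0.3, 0.5 and 0.7. The false-positive rates are:

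| Assumed shift x (SD) | rho 0.3 | rho 0.5 | rho 0.7 |
|---|---|---|---|
| 0 | 5% | 5% | 5% |
| 0.2 | 19% | 24% | 37% |
| 0.3 | 36% | 48% | 69% |

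Both x and rho are assumptions, because the protocol gives neither. The table shows how sensitive the contrast is if a shift exists; it does not estimate one.

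**The case against.** The strongest reply is that the exercise artefact is not in the document. Three reference rests are recorded in session 2 before RT1h, and two of them precede exercise in both arms. The protocol never says which one RT1h would use. A reader might infer that RT1h has no resting reference at all, or that it necessarily carries a post-exercise reference in EX. The text supports neither. This part of the reply stands: the arm-specific effect is conditional on the pre-adaptation rest being used, and an old reference does not by itself prove drift.

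The omission may also be a drafting slip, since every other set has a rest. That is plausible, but staff following the list as written would not record the rest, so the text needs correcting either way.

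The choice of reference could be left to a statistical analysis plan. A plan can choose among the rests that were recorded, but it cannot supply one that was not. The zero baseline described for the acquisition software does not fill the gap: it is set when signal quality is acceptable and is not described as a seated rest before RT1h.

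The scope is also limited. Behavioural rVMA outcomes are normalised to each child's baseline set and are untouched. O2.1 compares CON children only, so exercise cannot bias it; there the problem is the unequal reference age alone. Finally, the adaptation set's own rest follows exercise in EX, and a rest before RT1h does not change that.

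**Conclusion.** The point holds in limited form. As written, RT1h is the only rVMA set without a rest of its own, and its reference is at least 70.4 min old against about 0 min at RT24h and RT7d. Time effects on [O2Hb] in O2.1 and O2.2 are therefore confounded with reference age, whichever earlier rest is used. A spurious Exercise or Exercise x Time effect in O2.2 is a further possibility, but only if the pre-adaptation rest is the reference and still carries an exercise-related shift. The size of either bias cannot be derived from the protocol. The timing assumes the stated 2-second pace with no added pauses, which would only lengthen the gap. The change is worth making before data collection because it costs very little and a missing rest cannot be recovered afterwards.

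**What to change.** In the Optical neuroimaging section, add RT1h to the list of sets preceded by the 30-second seated rest, taken immediately before the set. In Data reduction, state that each retention set is normalised to its own preceding rest. All three Time levels then have a reference of about the same age, and no borrowed reference enters the Exercise x Time comparison. The cost is 30 seconds per child in session 2 and a line of text in each of the two sections.
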